### Adult Playfulness Trait Scale (APTS)

APTS is a 19-item self-report measure of adult playfulness. The APTS consists of three sub-dimensions: fun-seeking motivation (fun belief, initiative and reactivity), uninhibitedness and spontaneity. Multiple steps of conceptual evaluation have demonstrated adequate validity and reliability [20]. The APTS will be administered to staff before commencement of the intervention period.

### Video recording of uncertainty

The iPADs are used to video record any uncertain or ‘risky’ behaviours which occur on the playground. When children are viewed to be currently partaking in risky behaviour, or their behaviour looks like it could potentially become a risky situation, the children’s activities and behaviours are recorded on video. The video recording is performed by an unobtrusive member of the research team who does not interact with the children. The videos are then stored for future analysis, primarily looking at how the ‘risky’ situation is resolved (i.e. by an adult or by the child).

### Qualitative evidence

In-depth (~1 h), semi-structured interviews with parents and teachers nominated by principals are purposely selected to represent a range of opinions about the value of the program or tolerance of risk. Qualitative interviewing is an optimal way to understand the subjective experiences and world views of participants. We will adhere to accepted procedures to ensure trustworthiness of the data (e.g., triangulation. journaling) [21].

### Process evaluation

Researchers are present at the schools three to five days per week. In addition to observing the designated play space, they will have regular formal and informal conversations with school staff to ascertain the degree to which the intervention has been taken up (e.g., use of materials; teachers’ attitudes and beliefs) and monitor difficulties and particular successes.

### Outcome evaluation

Both quantitative and qualitative evaluation will occur. Quantitative: we will measure the effectiveness of the intervention for changing interactions and behaviours on the playground (primary outcome) and teacher’s tolerance for risk in play at the cluster level, as well as at an individual level. We will also measure children’s coping abilities, parents’ and staffs’ tolerance for risk in play and willingness to grant autonomy. We will use Wilcoxon signed-rank tests to compare net change from baseline values during intervention and non-intervention phases for cluster-level outcomes. We will analyse individual-level outcomes using multi-level modelling to examine the effect of the intervention, allowing for any period effect and adjusting for clustering by school. We will use intervention phase data for establishing the sustainability of the intervention and gains. We will compare outcomes at the end of the intervention with those at the end of the control phase for all six schools to test for within-school change, adjusted for clustering. Qualitative: We will conduct semi-structured interviews with four parents and two teachers from each program after they have been involved in the program one year. Adults will be selected purposively to represent a range of opinions about the value of the program. We will explore shifts in perceptions of risk, comfort with promoting manageable risk-taking and children’s abilities to assume responsibility. Data will be transcribed verbatim and subjected to constant comparative analysis to identify emergent themes according to Charmaz’s [22, 23] approach to social analysis.

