## Methods/Design

### Overall study design

We will employ a cluster repeated measures trial with six Sydney-area primary-school-based programs for children with disabilities. The control period will be undertaken first for two school terms, followed by two terms of the intervention period.

All of the ~300 children enrolled in the six programs, their teachers and parents will participate. Table 1 outlines the timeline for the study. All participating schools have agreed to have numbered children (by means of a numbered sticker on the back of their shirts) and support the workshops and inventories. Schools will continue with normal recess and physical education. There are no exclusion criteria, however video, Coping Inventory data and identified observations will only be collected from consenting children. Staff will also provide consent to participate in the study and complete the Coping Inventories and Adult Playfulness Trait Scale (APTS).

**Table 1 Tab1:** Outcome variables in relation to hypotheses

Outcome Variables	Hypotheses: Significant increases in:
Adults’ promotion of manageable risk taking and children’s increasingly responsible actions on the playground	Ratio of time spent in positive play transactions^a^ to time spent in negative transactions^b^ (primary measure derived from modified SOPLAY described below).
Perceptions of parents and teachers regarding manageable risk taking and children’s abilities to assume responsibility	Positive opinions and stories expressed in interview
Child coping ability	Mean scores on the Coping Inventory^23^
Parents’ and teachers’ comfort with children taking manageable risks	Mean scores on the Tolerance of Risk in Play Scale (TRiPS)^15^ and a revised Willingness to Grant Autonomy Scale^21^

^a^adults may facilitate or join the play

^b^(e.g., aimless wandering or where adults stop or redirect)

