### Intervention phase

The intervention comprises two arms. 1) Risk-reframing- teachers and parents will participate together in small group intervention sessions focusing on the benefits of manageable risk-taking (including vigilance and taking increasingly greater responsibility for one’s own actions), the consequences of preventing children from engaging in manageable risk-taking, and strategies for making everyday risks manageable. Each program will engage in three two-hour sessions during the intervention phase. The first session will coincide with the introduction of the play materials. The second session will follow approximately 3–4 weeks after the first session. The third session will be implemented in the final weeks of the intervention period. Sessions will be scheduled to maximise attendance and multiple sessions in each school may be required. 2) Introduction of play materials. Materials without defined purposes, which are also considered facilitative of social cooperation, will be introduced to the school playground for children to use at all break times. Materials will conform to Australian standards and meet seven additional criteria: 1) no obvious play value; 2) encourage cooperative, gross motor play; 3) have multiple uses; 4) can be used in challenging, creative and uncertain ways; 5) provide interesting sensory experiences (e.g., from touch or movement); 6) any hazards inherent to the materials can easily be identified and managed by a child; and 7) are, or are made from, recycled materials. New materials will be introduced periodically to replace broken items and complement existing materials. Teaching staff will be asked not to intervene in the play unless children are at risk of imminent harm. Maintenance of the materials will be the responsibility of researchers in collaboration with staff from each program.

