### Playground observation system

During control and intervention periods, 3 to 5 days per week, we will record the activities and social interactions in which children and adults engage in the playground during lunch and recess periods. We use a purpose-built iPad application modified from the System for Observing Play and Leisure Activity in Youth (SOPLAY) [17]. We will train observers and check reliability against a gold standard observer. We will use these findings to calculate the primary outcome: quality of play and social interactions on the playground. This will be assessed by looking at the ratio of positive play transactions to time spent in negative play, through data collected from the SOPLAY observations. No observations will take place during rainy weather or at any other time when play is conducted indoors.

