### Coping inventory [18]

An observation instrument used to assess the skills and resources a child uses to meet personal needs and adapt to the demands of the environment. The CI is a 48-item scale completed by teachers at the beginning and end of each study phase. Factor analysis revealed evidence for one factor accounting for 75 % of the variance; high correlation with school achievement (California Achievement Tests; *r =* .71); significant but low correlations with self concept (Piers Harris; *r* = .17); inter-rater reliability *r =* .90–.92 and internal consistency α–.84–.98; *SEm* ≈ .03 [18]. We have established evidence for test–retest reliability (intra-class correlation = .96).

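### Intervention-phase data can describe maintenance of playground change during delivery; they cannot establish sustainability once research support ends

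*Protocol article*

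**What the plan says.** The quantitative part of the Outcome evaluation section commits to this: "We will use intervention phase data for establishing the sustainability of the intervention and gains". It then compares the end of the intervention with the end of the control phase in all six schools.

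The Overall study design section sets the calendar: "The control period will be undertaken first for two school terms, followed by two terms of the intervention period". No later phase is described.

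The Intervention phase section describes what is running during those last two terms:
- The materials "will be introduced to the school playground for children to use at all break times".
- They are renewed: "New materials will be introduced periodically to replace broken items and complement existing materials".
- Upkeep is shared: "Maintenance of the materials will be the responsibility of researchers in collaboration with staff from each program".
- On the workshops: "The third session will be implemented in the final weeks of the intervention period".

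The Process evaluation section adds that researchers are at the schools three to five days a week.

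On measurement, the Playground observation system section says: "During control and intervention periods, 3 to 5 days per week, we will record the activities and social interactions". The Coping inventory section says: "The CI is a 48-item scale completed by teachers at the beginning and end of each study phase". The TRiPS section places that scale at the start and end of the intervention phase.

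**The concern.** Sustainability has two halves in the plan's sentence: the gains and the intervention. In ordinary use, the first asks whether children and adults keep what they gained after the program team has gone. The second asks whether schools keep the program running by themselves. Both need observation after research support has ended or been reduced, and the sentence names data from a period in which that support is fully in place.

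This is not a detail that a condensed article leaves to a fuller document. The article names the data source for the claim. A statistical analysis plan could specify the model, but it could not make data collected during delivery describe the time after it.

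The stake is interpretation. The Economic evaluation section looks to a broader roll-out to similar schools, and the Discussion sees the results as possible evidence for policy-makers on standard practice. A reader in that position would take a reported sustainability result to mean that the program lasts without the research team.

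**Working it through.** No power, alpha or sample-size figure is involved, and the plan gives no figure to reproduce. The check lists each measure with a stated schedule and counts the time points inside and after the intervention phase.

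**Calendar.** 2 control terms + 2 intervention terms = 4 terms. Terms described after the intervention: 4 − 4 = 0.

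| Measure | Stated timing | Within the intervention phase | After it |
|---|---|---|---|
| Playground observation (primary) | Control and intervention periods, 3 to 5 days a week | Repeated throughout | 0 |
| Coping Inventory | Start and end of each phase | 2 points | 0 |
| TRiPS | Start and end of the intervention phase | 2 points | 0 |
| Adult Playfulness Trait Scale | Before the intervention | 0 | 0 |
| Willingness to Grant Autonomy Scale | Not given | Unknown | None stated |
| Interviews (qualitative) | After one year of involvement | Depends on when the year starts | Depends on when the year starts |

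**What delivery looks like at the last measurement.** Materials are still available at every break and still being renewed, researchers are still on site and share the upkeep, and the third workshop falls in the closing weeks. The end-of-intervention versus end-of-control contrast therefore estimates an effect under active delivery. It carries no information about withdrawal.

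**What each instrument can show within the phase.**
- *Playground observations.* Sampling on several days a week across two terms allows early and late parts of the phase to be compared. That bears on whether early change holds or fades under continued exposure.
- *TRiPS and Coping Inventory.* Two points give 2 − 1 = 1 change score. One change score cannot separate an early gain that held from a gain that came late, or from an early gain that partly faded. For these scales even maintenance during delivery cannot be shown.

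**Interviews.** Assuming a four-term school year, a year counted from the start of the control period ends with the intervention. A year counted from the start of the intervention ends about 4 − 2 = 2 terms after it. The article does not say which is meant. Either way, the interviews involve purposively chosen adults, (4 parents + 2 teachers) × 6 programs = 36 people, and they sit apart from the quantitative sustainability statement.

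**The case against.** The strongest reply is that sustainability is not defined and need not mean persistence after withdrawal. The materials are a change to the environment and would presumably stay in place if the program became standard practice. Whether gains hold with materials present is then a useful question. The observations are well placed to answer it: the second workshop comes about 3–4 weeks after the first and the third only near the end, so a stretch lies between them in which fading novelty could show. Process evaluation also follows uptake by staff. All of this stands for the playground outcome. It supports a claim of maintenance during delivery, which is narrower than what the sentence promises. It does not help TRiPS or the Coping Inventory.

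A second reply is that the full timetable may not be visible. The Overall study design section refers to Table 1 for the timeline, but the table shown lists outcome variables. That is a fair caution. A later phase in an unseen document would still leave this sentence naming the wrong data source.

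Third, the Discussion makes feasibility, efficacy and cost-effectiveness the conditions for policy use, and no hypothesis concerns sustainability. This stands, and it limits the weight of the point.

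Two stronger readings are tempting, and the article does not support them:
- *That no data bear on whether gains last.* The repeated observations do bear on it within the phase, and the interviews might fall after the intervention.
- *That end-of-phase scores are inflated by the late workshop.* The order of the third session and the final TRiPS and Coping Inventory is not given, and nothing in the article shows a short-lived rise. The third session is also one of three planned components, and measuring at the end of a planned intervention is ordinary.

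**Conclusion.** The point holds in limited form. As written, the plan would yield a conclusion on sustainability that its design cannot support: 0 of 4 described terms, and 0 scheduled measurements of the playground outcome, TRiPS or the Coping Inventory, lie after the intervention phase. The data can describe whether early change in playground observations is maintained or fades under continued delivery, and no more than that.

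This rests on two assumptions: that the phases described in the article are the whole schedule, and that readers will take sustainability to include what happens once research support ends. If the investigators meant only maintenance while the program runs, the defect is one of wording, but the wording still needs to change. The estimate of the intervention effect and its planned analyses are not affected. The sentence should be corrected before results are reported.

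**What to change.** Replace the sentence with:

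> We will compare playground observations between the first and second intervention terms to describe maintenance of effect during continued delivery; sustainability after withdrawal of research support is not assessed.

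The comparison is confined to the playground observations because TRiPS and the Coping Inventory have no intermediate measurement. It should be read as descriptive, since the two terms may also differ in season and in the children's development.

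The cost is one sentence. The comparison uses observations already planned, and nothing is added to the burden on schools. A later round of questionnaires alone would not restore the wider claim: it would leave out the primary outcome, which needs observers on site. Nor would it be cheap, with a 48-item teacher rating for up to about 300 children plus TRiPS from parents and teachers.

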### Economic evaluation

We will conduct an economic evaluation to compare the relative costs and outcomes associated with the intervention. A rigorous costing analysis will be undertaken, exploring the real world costs of implementing the intervention. This will include the small cost of providing the play materials and the larger cost of the risk-reframing sessions. The intention of doing this will be to estimate the financial implication of a broader roll-out of the approach to other similar schools, thereby supporting the translation of this novel research. For the cost-effectiveness analysis, the costs of providing the intervention will be contrasted with the incremental outcomes detailed previously (see Table 1), to provide some evidence for policy-makers to assess the feasibility of this interventional model. We do not believe that any benefit associated with the intervention would manifest in changing utility scores, hence we have not proposed a cost-utility analysis. We do however believe that the estimation of cost implications of the intervention forms a part of the appraisal of the approach.

## Discussion

New national programs, such as the National Disability Insurance Scheme, will provide support to people with disabilities by encouraging inclusion and access to mainstream activities and providing the framework to achieve their goals and aspirations. This initiative will allow people with disabilities to assume greater responsibility of their own daily lives. However, we need to ensure that young people with disabilities are suitably equipped to appropriately assume this responsibility that is expected later in life. Innovative approaches, such as the one we have proposed, are desperately needed, to prepare young people and their carers for a future of autonomy and independence. It is essential that the development of these skills is promoted in primary school aged children, to provide a foundation for life long attributes. This early intervention can occur by including children in age-appropriate ways and simultaneously addressing the issues of adults who have the most significant influence — parents and teachers. The research presented is an important step toward promoting choice and control for children with disabilities and by encouraging autonomy and responsibility may ultimately improve quality of life. If this research is shown to be feasible, efficacious and cost-effective, it may provide policy-makers with evidence to translate this model into standard practice in Australian schools.

## Abbreviations

APTS: adult playfulness trait scale
SOPLAY: system for observing play and leisure activity in youth
TRiPS: tolerance of risk in play
